### Justification for the EMA sample size

As the EMA is the most burdensome aspect of our study protocol, we carefully evaluated the feasibility of utilizing a subsample of the study population for this component. The primary objective of the EMA is to investigate the cross-lagged effects between sleep parameters and affect during therapy using a Random Intercept Cross-Lagged Panel Model (RI-CLPM). To determine the appropriate sample size for our analysis, we conducted a power analysis using the powRICLPM package in R, following the procedures outlined by Mulder (2023) [91]. The parameters for our analysis included 14 time points, an intraclass correlation coefficient (ICC) of 0.3, a correlation between random intercepts (RI_cor) of 0.3, a within-group correlation of 0.5, and expected effect sizes indicated by a correlation matrix with a moderate effect size of 0.4 for sleep and affect, as well as cross-lagged effects of 0.3. In our power analysis, we examined a sample size range from 100 to 231 participants, incrementing by 10, while employing 1000 Monte Carlo replications to ensure robust power estimates. The results indicated that a sample size of 120 participants would provide a power level of over 90%. As a result, we opted to include only 120 participants in the EMA component of the study. Following the data analysis, we will conduct a post hoc power analysis to evaluate the power of the RI-CLPM. If this analysis reveals insufficient power, we have the option to revert to a mixed model approach, which necessitates fewer participants to achieve similar power levels.

### Justification for the saliva sampling sample size

Saliva sampling is optional in the study protocol to reduce participation barriers. The main aim of the saliva sampling is to compare possible shifts in DLMO between conditions. A simulated dataset was created using the *simr* package in R, with a mean DLMO set at 23:00 and extensive between-person variance (*SD* = 120 min) and within-person variance (*SD* = 45 min). Using a mixed-effects model with a random intercept for participants, we simulated a sample of 72 participants measured at two timepoints (pre- and post-treatment). The analysis yielded a power of 96.40% (95% CI 95.05, 97.47) to detect a phase shift of 30 min in DLMO with an alpha level of 0.05. This high power suggests that even with the optional saliva sampling and a sample size of 72 we can confidently assess the effect of BLT on circadian rhythm changes.

### Justification for the MRI sample size

For the MRI assessments, our study will focus on a cohort of 60 participants recruited from LUBEC, as GGzE does not have the means to conduct MRI assessments. The main analysis of the brain data will involve a pre- vs. post-BLT comparison, without any comparisons among the three conditions (i.e., no between-subjects effect). A simple sensitivity power analysis, conducted using G*Power software for the intended statistical tests on the neuroimaging data (paired *t*-test), suggests that with a sample size of *N* = 60, we can achieve a power of 0.80 at an alpha level of 0.05, anticipating a small to medium effect size (Cohen’s *d* = 0.33), which aligns with findings from recent neuroimaging studies [59, 64, 66, 67].

Similar to the explorative subgroup analysis of the neuroimaging data comparing remitters and non-remitters will be based on past neuroimaging studies with a similar setting and having a sample size of minimal 20 participants per group [59]. This sample size is in adherence with recent publications in the field and accounts for the limitations encountered in a priori power size calculations of neuroimaging data [92, 93].

### Recruitment {15}

We intend to include participants year-round for approximately 2 years. The distribution of the recruitment burden is shared between two mental health clinics: GGzE’s aim is to include 171 participants, while LUBEC aims for 60. At GGzE, all individuals referred for BLT are approached for potential participation. Previous light therapy studies conducted at this center with the same enrolment strategy have achieved inclusion rates of approximately 100 participants per year. Given that this study is considered more extensive than previous research, we anticipate it will take approximately 2 years to reach the targeted enrolment of 171 participants. At LUBEC, BLT is offered for the first time, and only in conjunction with study participation. Recruitment efforts involve the collaboration with primary care and secondary mental health institutions for the referral of patients.

The rate of participant accrual is reviewed every half year. The number of participants who consented but did not qualify and the number of qualified, enrolled participants who dropped out will also be examined to detect patterns of insufficient recruitment rates. These will be addressed with modified recruitment strategies so that we can meet our recruitment goals.

## Assignment of interventions: allocation

### Sequence generation {16a}

Eligible participants are randomized using block randomization via the Research Manager data platform [94]. To ensure a balanced distribution among treatment groups and minimize potential biases, participants are stratified based on several key factors, including chronotype (categorized as early, intermediate, or late based on the MEQ [86], clinical diagnosis (differentiating between unipolar and bipolar conditions according to the M.I.N.I. assessment), and participation in the melatonin assessment (indicated as either yes or no).

### Concealment mechanism {16b}

A randomization table was generated using ResearchManager before the start of the trial. Access to the randomization table is restricted for the whole research team and can only be accessed by an independent researcher of the Eindhoven University of Technology not affiliated with the study. The randomization process in ResearchManager employs permuted block randomization with blocks of six to maintain balanced allocation across study groups.

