**Methods:**

This multicenter randomized controlled trial will enroll 231 patients with unipolar or bipolar depression, all currently experiencing a depressive episode. Participants will be randomized to one of three BLT interventions: (1) traditional home-based BLT, (2) BLT administered in the *LightCafé*—a novel setting promoting social interaction and lifestyle support, or (3) *LightCafé* BLT with personalized timing of both light and darkness by adding the use of blue light blocking glasses. The treatment duration will range from one to three weeks, based on preset definitions of participant’s response. The primary outcome is the change in depressive symptoms, assessed by a blinded rater. Secondary outcomes include subjective and objective sleep measures, circadian rhythm parameters from melatonin patterns and actigraphy, and functional outcomes. Change processes will be assessed using ecological momentary assessments of daily affect and energy levels, light exposure sensors, and via brain imaging.

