### Eligibility criteria {10}

#### General eligibility criteria

Eligibility will be assessed during the intake by study team members trained in administering the MINI International Neuropsychiatric Interview 5.0.0 (M.I.N.I.; [69]). The inclusion criteria are as follows:Age between 18 and 65.Diagnosis of unipolar or bipolar depression (seasonal or non-seasonal) confirmed by the M.I.N.I. [69].Currently experiencing a depressive episode, as indicated by a Quick Inventory of Depressive Symptomatology Self-Report (QIDS-SR; [70]) score of 6 or higher.Proficiency in either Dutch or English is required for questionnaire completion.

Participants are excluded from participation if they:Are currently experiencing a (hypo)manic or mixed episode, as determined by the M.I.N.I. assessment [69].Are presently in a psychotic episode, as determined by the M.I.N.I. assessment [69].Exhibit significant active suicidality, indicated by a score of 10 or higher on the M.I.N.I. module [69].Initiated antidepressant therapy (including medication, psychotherapy, BLT, or other specific depression treatments) within the last 2 months prior to study enrolment.Have a bipolar disorder but are currently not under mood-stabilizing treatment for at least 1 month at the recommended dosage.Have used melatonin or agomelatine in the past month.Are currently using antibiotics.Are currently taking medications that increase light sensitivity.Have travelled across more than one time zone in the past month or during the treatment period.Have travelled to sunny holiday destinations or engaged in outdoor winter sports in the past month.Have pre-existing eye and skin disorders such as retinitis pigmentosa, porphyria, chronic actinic dermatitis, and sun-induced urticaria.Have systemic disorders with potential retinal involvement, such as rheumatoid arthritis and systemic lupus erythematosus.Have color blindness (based on self-report).Worked night shifts within the last three months.Suffer from (retinal) blindness, severe cataracts, or glaucoma.Experience light-induced migraine or epilepsy.Are currently pregnant or have a child Younger than 18 months old.

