### Implementation {16c}

All study participants are entered into ResearchManager during intake, and upon confirmation of eligibility and completion of intake questionnaires, they are randomized using the program’s algorithms. This process can be conducted by any member of the study team, including principal investigators, researchers, or study interns. During enrollment, researchers simply click a randomization button within ResearchManager, which then automatically assigns the participant to a study arm according to the randomization table.

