## Assignment of interventions: blinding

### Who will be blinded {17a}

Participants, researchers, and care providers are informed about the allocated interventions. However, to maintain impartiality in evaluating depressive symptoms, the primary outcome assessors are kept blind to both the treatment arm and the assessment time. These assessors have no other role in the study and, therefore, will remain unaware of the study’s design and possible interventions.

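### A single published block size of six weakens allocation concealment in an open-label trial: staff tallying allocations by stratum across both clinics could foresee up to about 17–20% of them

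*Protocol article*

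**What the plan says.** **Block size.** Concealment mechanism {16b} states: "The randomization process in ResearchManager employs permuted block randomization with blocks of six to maintain balanced allocation across study groups". It gives one size and no variation. The same section closes the pre-generated table to the whole research team; only an independent, unaffiliated researcher can open it.

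**Strata.** Sequence generation {16a} stratifies by chronotype (three levels), unipolar or bipolar diagnosis (two levels) and "participation in the melatonin assessment (indicated as either yes or no"). That makes 3 × 2 × 2 = 12 strata. Centre is not listed.

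**Who decides and who sees.**
- General eligibility criteria: "Eligibility will be assessed during the intake by study team members trained in administering the MINI International Neuropsychiatric Interview" (the M.I.N.I.).
- Implementation {16c}, on randomising: "This process can be conducted by any member of the study team, including principal investigators, researchers, or study interns". This happens after eligibility is confirmed and the intake questionnaires are complete.
- Who will be blinded {17a}: "Participants, researchers, and care providers are informed about the allocated interventions". Only the MADRS raters are blind.

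**Timing.** Trial status says the trial was still enrolling when the article appeared, having started in February 2024 with about two years of recruitment planned.

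**The concern.** Restricting the table protects the file. In an open trial with one known block size, however, past allocations within a stratum reveal what is left of the current block. The last place is always determined, and the fifth sometimes is. The people who could do this tally also run the intake and confirm eligibility, and they know all three stratum values before randomising. One of those values, melatonin participation, is an optional choice made by the patient.

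A team member who can foresee the next arm may, without intending to, encourage, delay or discourage a particular patient. That changes who enters each arm. Blinded rating protects how the outcome is measured, not the composition of the arms, and an intention-to-treat analysis keeps whatever composition results. The trial looks for small differences between three active arms, so even a modest tilt in prognosis would matter.

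**Working it through.** **Inputs.** Three arms (Abstract: "Participants will be randomized to one of three BLT interventions"); block size 6 {16b}; 12 strata {16a}; 231 patients, SD 13.2 and assumed effects −0.25, −0.33 and −0.40 (Sample size {14}); 72 in the melatonin subset; centre targets 171 and 60 (Recruitment {15}). Assumptions of mine: 1:1:1 allocation, because the ratio is not printed and only "with blocks of six to maintain balanced allocation across study groups" points to it; and, for uneven strata, chronotype 20/50/30% and 20% bipolar. The plan gives no predictability figure to reproduce.

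**Step 1: certainty in one complete block.** Two places for each of three arms give 6!/(2!2!2!) = 90 equally likely orders.

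| Position | 1 | 2 | 3 | 4 | 5 | 6 | Mean |
|---|---|---|---|---|---|---|---|
| Arm certain | 0 | 0 | 0 | 0 | 0.20 | 1.00 | 0.200 |
| At least one arm excluded | 0 | 0 | 0.20 | 0.60 | 1.00 | 1.00 | 0.467 |
| Best guess correct | 0.333 | 0.400 | 0.500 | 0.533 | 0.600 | 1.000 | 0.561 |
| Home versus café known | 0 | 0 | 0.067 | 0.200 | 0.467 | 1.000 | 0.289 |

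The fifth place is certain when the last two places belong to the same arm: 3 × 1/15 = 1/5. So (1/5 + 1)/6 = 20% are certain. Chance guessing would be right 33% of the time.

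**Step 2: the trial's size and strata.** Simulating 231 patients, with unfinished last blocks:
- one stratum: 19.7% certain;
- 12 strata, equal or uneven: 17.5% (95% range 15.6–19.9%), and 0.175 × 231 ≈ 40 patients. Home versus café is known for 26%, and the best guess is right 54% of the time;
- 24 strata, if centre were added: 15.7%.

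**Step 3: staff who see only their own clinic.** Blocks run across centres, so such staff do not know where a block starts or which places the other clinic has used. A running count of own-site allocations in each stratum guesses correctly about 41% of the time: above 33%, but well below 54%.

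**Step 4: possible tilt.** Home is excluded for 22.2% of allocations and certain for 6.7% (sum 28.9%). Among café patients the known share is 0.222/0.667 = 0.333; among home patients it is 0.067/0.333 = 0.20. If known-café patients are shifted by +d and known-home patients by −d in prognosis, the café-minus-home tilt is 0.333d + 0.20d = 0.533d in complete blocks, and 0.48d in the 12-stratum simulation.
- d = 1 (a 2-point gap): 0.48 points; 0.48/13.2 = 0.04 SD.
- d = 2 (a 4-point gap): 0.96 points; 0.96/13.2 = 0.07 SD.

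The plan's assumed advantages over home are 0.33 − 0.25 = 0.08 (LightCafé) and 0.40 − 0.25 = 0.15 (LightCafé+), read here as SD units. The gap d is my assumption; nothing in the documents fixes it.

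**Step 5: varying block sizes.** For an observer who knows the set of sizes but not the order, certain knowledge falls from 20% to 5.4% (sizes 6/9), 3.9% (3/6/9) or 2.4% (6/9/12). Best-guess success falls much less: 56% to 53–55% in complete blocks, and about 54% to 51% for a running count in 12 strata with 6/9/12.

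**The case against.** The strongest reply is that the plan has real safeguards. The table is held outside the team, the platform assigns only after eligibility is confirmed, all referred patients are invited, and entry rests on a structured interview and a self-report cut-off. Foreseeing an allocation requires a tally by stratum across two clinics, and no section says staff at one clinic see the other's allocations. All of this stands. A reader might infer that concealment fails outright; the documents do not support that, since at least about four in five allocations cannot be known with certainty even by the best-placed observer.

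A reader might also infer that the plan credits its blocking with minimising bias and so contradicts itself. It does not: Sequence generation {16a} gives that aim to the stratification.

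The primary model, as described, has timepoint and timepoint-by-arm terms without a separate arm term, so selection on baseline severity would be at least partly absorbed. That too stands, but selection on prognosis not captured by baseline MADRS would remain, and the other covariates named (age, sex, credibility and expectancy) would not correct it.

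Finally, on the stated timetable few blocks may be left to change. That limits the benefit of a new list, but not of a check on the allocations already made.

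**Conclusion.** The weakness is real and moderate. One fixed, published block size in an open-label trial, with eligibility and randomisation in the hands of the same unblinded team, makes up to about 17–20% of allocations foreseeable. This is an upper bound. It assumes 1:1:1 allocation and a running tally in every stratum across both clinics, and it is lower for staff who see only their own site.

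Whether any bias has resulted is unknown, and nothing in the documents suggests staff have used the pattern. The tilt figures (about 0.5 points for a 2-point gap, about 1 point for a 4-point gap) show what would be needed; they are not estimates. They matter because the smaller arm difference the plan assumes is itself only 0.08. This is an inexpensive improvement worth making, not a flaw that invalidates the comparison.

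**What to change.** 1. For blocks not yet opened, have the independent table holder regenerate the list with block sizes that vary at random in multiples of three (for example 6, 9 and 12) and are not disclosed to the study team. Amend Concealment mechanism {16b} to say that sizes vary, without listing them.
2. State in Implementation {16c} that chronotype category, diagnosis and melatonin participation are recorded and fixed before the randomise button is pressed, with no later change of stratum.
3. For allocations already made, add a sensitivity analysis: compute each patient's predicted probability of each arm from earlier allocations in the stratum, test whether intake QIDS-SR depends on it, and refit the primary model without the allocations that were certain. Intake QIDS-SR suits this because it is collected before randomisation, whereas the baseline MADRS comes afterwards.

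**Cost.** A new list, a short amendment and one analysis on data already collected; no extra patients. An unfinished block of 12 can leave two arms in a stratum apart by up to four patients, against two now. Best-guess success falls only modestly (about 54% to 51%), although certain knowledge falls to about 2–5%. Step 2 stops changes of stratum after the entry is made, but not encouragement or delay before it. If few blocks remain, step 3 carries most of the value.

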### Implementation {16c}

All study participants are entered into ResearchManager during intake, and upon confirmation of eligibility and completion of intake questionnaires, they are randomized using the program’s algorithms. This process can be conducted by any member of the study team, including principal investigators, researchers, or study interns. During enrollment, researchers simply click a randomization button within ResearchManager, which then automatically assigns the participant to a study arm according to the randomization table.

## Assignment of interventions: blinding

### Who will be blinded {17a}

Participants, researchers, and care providers are informed about the allocated interventions. However, to maintain impartiality in evaluating depressive symptoms, the primary outcome assessors are kept blind to both the treatment arm and the assessment time. These assessors have no other role in the study and, therefore, will remain unaware of the study’s design and possible interventions.

### Procedure for unblinding if needed {17b}

N/a—all parties that could benefit from unblinding are already unblinded.

## Data collection and management

### Plans for assessment and collection of outcomes {18a}

#### Questionnaires

Several questionnaires are sent to the participant via ResearchManager at various timepoints in the study. An overview of these questionnaires, including the constructs they measure and the corresponding time points, is provided in Table 1. Each of these instruments has demonstrated well-established reliability and validity, ensuring their effectiveness in accurately measuring the intended constructs. To maintain high data quality, our research staff undergoes specialized training by experts, focusing on the consistent administration of the MADRS, M.I.N.I., and YMRS. Furthermore, we routinely assess inter-rater reliability for each MADRS administrator to ensure the accuracy and consistency of the assessments.

The following questionnaires and rating scales will be used during the study:**Mini-International Neuropsychiatric Interview (M.I.N.I.) PLUS 5.0** [69]: The M.I.N.I. is a brief, structured diagnostic interview designed to generate DSM-5 psychiatric diagnoses in approximately 30 min. It covers mood disorders (bipolar I & II, major depression, suicidality), anxiety disorders (social anxiety, panic, agoraphobia, generalized anxiety, PTSD, OCD), ADHD, eating disorders (anorexia, bulimia), substance use disorders (alcohol and other substances), and psychotic disorders. Its modular format allows rapid, reliable case‐finding in clinical trials and epidemiological studies. Test–retest reliability coefficients for major depression and anxiety diagnoses typically exceed *κ* = 0.70, and it shows good concordance with longer interviews such as The Structured Clinical Interview for DSM-5 [95]**Montgomery–Åsberg Depression Rating Scale (MADRS)** [78]: The MADRS is a clinician‐administered 10-item scale that quantifies depressive symptom severity over the preceding week. Each item (e.g., apparent sadness, inner tension, sleep, and appetite disturbances) is rated 0–6, yielding a total score from 0 to 60. The MADRS exhibits excellent inter‐rater reliability (ICC > 0.90) and sensitivity to treatment-induced change, making it a standard in antidepressant trials.**Quick Inventory of Depressive Symptomatology–Self-Report (QIDS-SR)** [70]: The QIDS-SR comprises 16 items mapping the nine core DSM-5 depressive domains (sad mood, anhedonia, concentration, self‐view, suicidal ideation, energy, sleep, appetite/weight, psychomotor changes) over the past 7 days. Responses use a 0–3 Likert scale, with composite scoring algorithms yielding a 0–27 total. Internal consistency is high (Cronbach’s *α* = 0.86–0.89), and the QIDS-SR correlates strongly with both the MADRS and HAM-D (*r* > 0.80), supporting its validity as a brief self‐report measure of depression severity.**Morningness–Eveningness Questionnaire (MEQ)** [86]: This 19-item self-report evaluates an individual’s circadian preference—“chronotype”—by asking about preferred timing for sleep, wakefulness, and peak performance. Scores classify respondents from “definite evening type” to “definite morning type.” The MEQ demonstrates good internal consistency (*α* ≈ 0.80) and has been validated against objective markers such as dim‐light melatonin onset.**Ultra-Short Munich Chronotype Questionnaire (μMCTQ)** [87]: The μMCTQ estimates chronotype via six items: usual sleep onset andsimi of work versus free days. By calculating the midpoint of sleep on free days corrected for accumulated sleep debt, it yields an estimate of intrinsic circadian phase. Test–retest reliability for sleep timing variables exceeds *r* = 0.90, and μMCTQ midpoints correlate well with full MCTQ scores.**Pittsburgh Sleep Quality Index (PSQI)** [84]: The PSQI is a 19-item self-report assessing sleep quality and disturbances over the past month across seven domains: subjective sleep quality, latency, duration, habitual efficiency, disturbances, medication use, and daytime dysfunction. Global scores > 5 indicate poor sleep. The PSQI’s internal consistency is acceptable (*α* = 0.75–0.83), and it discriminates insomniacs from healthy controls with a sensitivity of 89.6% and specificity of 86.5%.**Insomnia Severity Index (ISI)** [85]: The ISI consists of seven items rated 0–4 that probe the severity, impact, and perceived distress of insomnia symptoms. Total scores range from 0 to 28, with higher scores reflecting more severe insomnia. Internal consistency is excellent (*α* = 0.90), and the ISI correlates strongly with sleep diary metrics and polysomnographic indices, validating its use as a brief screening and outcome measure.**Consensus Sleep Diary(CSD)** [77]: A standardized daily log, the Consensus Sleep Diary captures subjective sleep–wake parameters—sleep onset latency, wake after sleep onset, total sleep time, time in bed, number and duration of awakenings, and morning sleep quality/refreshed ratings. It is the recommended unifying sleep diary for research, showing excellent agreement (*r* > 0.80) with actigraphy and flexibility for both EMA and weekly retrospective summary at follow‐up visits [77].**Short Form Health Survey (SF-12)** [82]: Derived from the SF-36, the SF-12 yields two summary scores—Physical Component Summary (PCS) and Mental Component Summary (MCS)—from 12 items covering domains such as physical functioning, role limitations, bodily pain, vitality, social functioning, and mental health. Despite its brevity, the SF-12 explains over 90% of the variance in SF-36 summary scores, exhibiting high test–retest reliability (ICC > 0.70) and construct validity across diverse populations.**Mental Health Quality of Life (MHQoL)** [83]: The MHQoL is a seven-dimension, four-level descriptive system (MHQoL-7D) plus a visual analogue scale (MHQoL-VAS, 0–10) for overall psychological well-being. Dimensions include self-image, independence, mood, relationships, daily activities, physical health, and outlook. It demonstrates good feasibility, content validity for mental health populations, and sensitivity to clinical change.**Credibility/Expectancy Questionnaire (CEQ)** [71]: The CEQ measures perceived treatment credibility and expectancy via six items: three assess credibility on a 1–9 scale and three assess expectancy on a 0–100% scale. Internal consistency ranges from *α* = 0.79 to 0.90, and early expectancy ratings predict clinical outcomes across psychotherapy and pharmacotherapy trials, underscoring its utility as a prognostic indicator.**Young Mania Rating Scale (YMRS)**: The YMRS is an 11-item clinician interview that quantifies manic symptoms—elevated mood, sleep, irritability, speech, thought content, motor activity, and insight. Items are weighted according to severity and duration (total score 0–60). Inter‐rater reliability is excellent (ICC > 0.85), and sensitivity to mood changes renders the YMRS a benchmark for bipolar disorder trials [74].**Adverse Event Scale for Light Therapy***:* A custom checklist will record the presence, frequency, and severity of known side effects of bright light exposure (e.g., headache, eyestrain, nausea), using Likert‐type ratings to facilitate systematic monitoring of tolerability throughout the intervention period.

**Table 1 Tab1:** Overview of the questionnaires administered at different stages of the study

